### Measures

The primary and secondary outcome measures will be collected via CATI at 1, 6 and 12 months post-discharge.

#### Primary outcome measures

The primary outcome measure will be abstinence from smoking, both 7-day point prevalence and prolonged abstinence. Participants who report being abstinent from smoking for 7 days or greater will be required to submit a breath sample to validate their quit attempt. CATI interviewers will organise a time to carry out this procedure and project staff, blind to allocation group, will meet participants in a public place or their home as soon as can be arranged to verify abstinence. Breath samples will be taken using a Micro^+^ Smokerlyser (Bedfont Scientific Ltd,
http://www.bedfont.com/smokerlyzer), where the exhaled carbon monoxide level must not exceed 6.99 ppm for the self- reported abstinence to be considered valid
[50,51].

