[30-32]. Systematic review evidence from general medical settings suggests that multimodal post-discharge cessation support of at least 4 weeks in length or greater can result in higher rates of successful smoking cessation
[17].

A recent randomised controlled trial has demonstrated the effectiveness of linking mental health inpatients to community-based smoking support following discharge. Prochaska and colleagues
[20] reported a significant difference in point prevalence abstinence at 18 months post-discharge; 20% and 7.7% for intervention and control conditions, respectively. Over a period of up to 6 months post-discharge, intervention group participants were able to take up both pharmacological (NRT for a total duration of up to 10 weeks) and psychosocial (face-to-face, computer-based, and self-directed reading) smoking cessation support, tailored to their readiness to stop smoking. An opportunity may exist to enhance and extend such positive findings by providing multi-modal smoking cessation support to all smokers, proactively and intensively, immediately following discharge, regardless of assessed readiness to change.

To assess the feasibility of such an approach we conducted a pilot randomised controlled trial of an intervention consisting of the provision of psychological and pharmacological support to smokers admitted to one inpatient psychiatric facility. Inpatient smokers were randomly allocated to a multimodal smoking cessation intervention or treatment-as-usual control. Smoking cessation treatment was initiated for all smokers during admission and continued for a 4-month period post-discharge with assessments made at 1 week and at 2, 4 and 6 months
[33]. At the end of treatment (4 months), participants in the intervention group had significantly higher rates of 7-day point prevalence abstinence than controls (11.5% versus 2%), but this difference was not sustained at 6 months follow-up
[34]. Based on the findings of these previous studies, the objective of this study is to conduct a randomised controlled trial to test the effectiveness of a multi-modal smoking cessation intervention, initiated within mental health inpatient facilities for all smokers and continued post-discharge, on 12-month post-discharge smoking cessation rates.

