**Figure 1 F1:**
[figure not shown]
**Study design.** ASAP, as soon as possible; CATI, computer-assisted telephone interview; NRT, nicotine replacement therapy.

Follow-up assessments will be conducted at 1, 6 and 12 months post-discharge for both conditions. The primary outcome measures comprise 7-day point prevalence of smoking abstinence and prolonged smoking abstinence. Secondary outcome measures will include number of cigarettes smoked per day, nicotine dependence, quit attempts, and readiness to change smoking behaviour. The effect of the intervention will be assessed by comparing primary and secondary outcome measures between intervention and control groups at each follow-up point.

Ethics approval for the study has been obtained from the Hunter New England Human Research Ethics Committee, HNEHREC reference no.: 11/12/14/4.02, and the University of Newcastle Human Research Ethics Committee, reference no.: H-2012-0061. The trial is registered on the Australian New Zealand Clinical Trials Registry ACTRN12612001042831. Date registered: 28 September 2012.

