### Randomisation, allocation concealment and sequence generation

A random allocation sequence using permuted block randomisation (with a block size of ten) will be generated by a statistician independent of the project prior to the commencement of recruitment. Randomisation will be carried out separately by site and stratified by diagnosis type to account for differences in smoking levels and nicotine dependence (psychosis/non-psychosis type diagnosis)
[5,35]. Participant allocation to group (1:1 ratio) will occur immediately post-baseline data collection. Research staff will provide participants with a sequentially numbered, opaque, sealed envelope. The envelope will contain a coloured piece of paper that indicates allocation to either the Supported Care or Normal Care condition. Research staff involved in recruitment and outcome data collection will be blind to the order of patient condition assignment.

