### Sample size

Considering 80% power with a 5% significance level, 332 participants per group will be required to detect a 4% difference (1% versus 5% for Normal and Supported Care participants, respectively) in prolonged abstinence at 12 months post-discharge. This sample size will also be adequate to detect a 10% difference in point prevalence abstinence at 12 months post-discharge
[20].

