#### Analysis of primary outcome measures

A linear model with estimation via Generalized Estimating Equations, using the logit link function given the dichotomous outcome variable, will be used to examine abstinence versus smoking status at 12 months by condition. The data collected at 1 and 6 months will also be examined; however, the 12-month follow-up will be the primary focus. Generalized Estimating Equations, a multivariate extension of generalised linear models, accounts for dependence of responses within individuals due to repeated measures. Any covariates identified in preliminary data analyses may be added to the model. Subgroup analyses will be considered, likely by dependence and diagnosis (psychosis versus non-psychosis)
[5,57]. All analyses will be conducted using intent-to-treat principles, with participants retained in their originally assigned groups
[58].

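### Two co-equal primary abstinence outcomes at 12 months have no rule for success, so the stated 5% level is exceeded if a win on either one counts

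*Protocol article*

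**What the plan says.** The section on primary outcome measures reads: "The primary outcome measure will be abstinence from smoking, both 7-day point prevalence and prolonged abstinence". The Abstract and the text after Figure 1 list the same two measures as primary, in the plural and without ranking them.

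The Sample size section gives the only significance level in the article: "Considering 80% power with a 5% significance level, 332 participants per group will be required to detect a 4% difference", the rates being "1% versus 5% for Normal and Supported Care participants, respectively) in prolonged abstinence at 12 months post-discharge". It continues: "This sample size will also be adequate to detect a 10% difference in point prevalence abstinence at 12 months post-discharge". No second significance level and no control rate accompany that sentence.

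On timing, the section on the analysis of primary outcomes says: "The data collected at 1 and 6 months will also be examined; however, the 12-month follow-up will be the primary focus". The text after Figure 1 is looser and has the effect assessed by "comparing primary and secondary outcome measures between intervention and control groups at each follow-up point". The primary analysis is one type of model, with a logit link and generalised estimating equations, for abstinence against smoking. It does not say which abstinence measure decides the trial.

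**The concern.** With two primary outcomes and no rule for combining them, the article does not define a positive trial. A significant result on one measure alone could be reported as success, and each test would have had its own chance of a false positive.

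A split result is plausible. The two measures are planned at very different levels: prolonged abstinence at 1% against 5%, and point prevalence with a 10-point difference. Power differs too. At 332 per group and two-sided 5%, without continuity correction, it is about 86% for prolonged abstinence. For a 10-point difference in point prevalence it is 95% to 97% if the control rate is 10% or 7.7% (the control rate quoted in the Background from an earlier trial). If only point prevalence is significant, the article does not say what the trial has shown.

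**Working it through.** **1. Reproduce the sample size.** Inputs from the Sample size section: p1 = 0.01, p2 = 0.05, power 80%, level 5%. Allocation is 1:1 (Randomisation section). Sidedness is not stated. With mean rate 0.03:

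n = [1.96·√(2·0.03·0.97) + 0.8416·√(0.01·0.99 + 0.05·0.95)]² / 0.04² = (0.4728 + 0.2016)² / 0.0016 ≈ 284.3

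With continuity correction: n/4 · [1 + √(1 + 4/(n·0.04))]² = 71.08 · (1 + 1.1626)² ≈ 332.4.

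This matches the stated 332. Other versions do not: 285 two-sided without correction, 224 one-sided, 272 one-sided with correction, 282 unpooled, 250 arcsine. So 332 uses the whole two-sided 5% on prolonged abstinence.

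**2. Error if either outcome suffices, tests at nominal size.** Assume that anyone with prolonged abstinence also counts as abstinent at 7 days, and that each outcome is tested at two-sided 5%. For rates p (prolonged) and q (point prevalence), the correlation is r = √[p(1−q) / (q(1−p))]. The chance that at least one |z| exceeds 1.96 comes from the bivariate normal distribution. The rates are assumptions.

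| p, q | r | Either significant, nominal-size tests | Either significant, Wald logit, 332 per arm |
|---|---|---|---|
| 1%, 20% | 0.20 | 9.6% | 5.5% |
| 1%, 10% | 0.30 | 9.5% | 5.3% |
| 3%, 15% | 0.42 | 9.3% | 8.1% |
| 5%, 15% | 0.55 | 8.9% | 8.4% |

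Independent tests would give 1 − 0.95² = 9.75%, and the Bonferroni bound is 10%.

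**3. Error with actual tests.** The last column simulates nested outcomes with 332 per arm and no treatment effect, counting arms with zero events as non-rejections. At a 1% rate the Wald logit test is very conservative: its true size is about 0.6%, so it adds little to the error from point prevalence. An uncorrected score test in the same four settings gives about 9.0% to 9.3%.

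These four pairs show the range but are not strict bounds. At (5%, 10%), for example, r = √(0.05·0.90 / (0.10·0.95)) = 0.69, and at r = 0.7 the nominal-size figure is 8.3%.

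**4. Error if both must succeed.** It cannot exceed the level of either test, so it is at most 5%.

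**5. What a split would cost.** At 2.5% per outcome (critical value 2.241), the formula in step 1 gives 345 per group, or 393 with continuity correction.

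| Power for 1% v 5% | 332 per group, 5% | 332 per group, 2.5% | 400 per group, 2.5% |
|---|---|---|---|
| With continuity correction | 80% | 71% | 81% |
| Without correction | 86% | 78% | 86% |
| Wald logit | 83% | 74% | 84% |

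**The case against.** The strongest reply has four parts.

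First, this is a condensed article and the statistical analysis plan is not shown, so rules on multiplicity may be there. That is right about the detail of any adjustment. It does not cover the choice and ranking of primary outcomes or the alpha behind the sample size, because the article fixes these itself. A later split would change the level behind 332, and an order or a single primary would change the outcome statement. A rule that both must succeed would leave 5% per test but would still have to be declared.

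Second, the article never says that either outcome suffices, and it speaks of one primary measure covering both. This stands: the inflation is conditional on the either-outcome reading. It is also an inference that each outcome is tested at 5%, since the analysis sections state no level.

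Third, the size depends on the test. This stands too. With a Wald test from a logit model and a 1% rate, the error is barely above 5%. The article does not say which test statistic will be used.

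Fourth, a split is affordable if all 400 per arm are analysed, for example with missing outcomes coded as smoking. That is true, so ordering is not the only valid remedy. With about 332 per group observed, a split loses power.

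A reader might also infer from the text after Figure 1 that all six comparisons (two outcomes at three times) are primary. The documents do not support this. The objective, both sample-size statements and the analysis section all point to 12 months, so the 1- and 6-month looks do not add to the primary error.

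**Conclusion.** The point holds for the two outcomes at 12 months. The article names two equal primary measures, uses its only stated level in full to size one of them, and gives no rule for declaring success.

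If either outcome can carry the trial, the false-positive risk exceeds the stated 5%: about 9% to 9.6% for tests near nominal size, and about 5.3% to 8.4% with a Wald logit test at 332 per arm. These figures rest on nested outcomes, an unsplit two-sided 5% for each test, and assumed rates of 1-5% and 10-20% in the four pairs shown. If both outcomes are required, the risk stays at or below 5%.

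It would go too far to say without conditions that the error rate nearly doubles. That needs both the either-outcome reading and a test close to its nominal size, and the article fixes neither. The absence of a defined answer when the two outcomes disagree does not depend on these figures.

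**What to change.** Name prolonged abstinence at 12 months, the outcome that sets the 332 per group, as the single primary outcome at two-sided 5%. Test 7-day point prevalence at 12 months second, at two-sided 5%, and only if the first test is significant. This fixed sequence holds the overall error at 5% and leaves the sample size unchanged.

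As a separate wording point, bring the text after Figure 1 into line with the analysis section by labelling the 1- and 6-month comparisons as secondary.

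The cost is revised wording in the outcome, sample-size and analysis sections and a registry update, with no extra participants. The Trial status section shows follow-up still under way, so the rule can be set before the outcomes are analysed. The downside is that point prevalence supports no confirmatory claim if prolonged abstinence is not significant.

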#### Secondary outcome measures

Secondary outcome measures will include number of cigarettes smoked per day, quit attempts made (number, duration, and supports used), nicotine dependence (assessed using the Fagerstrom Test for Nicotine Dependence)
[47], and motivation and readiness to quit (Readiness and Motivation to Quit Smoking Questionnaire)
[52].

### Process measures

#### All participants

Details regarding the delivery of any smoking-related care and/or support, received during the initial and any subsequent hospital admissions, will be collected by CATI staff at each of the three follow-up points.

#### Supported care participants only

As part of the motivational interview administered following assignment to supported care, participants will be asked to rank on a scale from 1 to 10 both importance of, and confidence to, quit smoking. To assess the degree of Supported Care intervention delivery, descriptive data will be collected during support calls by the designated support caller, including: the receipt and usage of discharge NRT pack; contact with, and perceived effectiveness of, Quitline support (if applicable); intensity and duration of support calls; dose, type, amount, usage and perceived effectiveness of NRT; side effects of NRT use; and nicotine withdrawal symptoms. Data assessing the degree of participant satisfaction with the intervention will also be collected by CATI interviewers after the completion of the 12-month follow-up.

#### Patient characteristics

Demographic and clinical information including age, gender, marital status, mental health diagnosis (primary and secondary), and Aboriginal and/or Torres Strait Islander status will be collected by recruitment staff from patient medical records, after the completion of the baseline interview. Education levels, employment status, identity as a smoker (items based on the PRIME theory of addiction
[53]), and levels of perceived support to quit smoking from partner, family, friends, and relevant health professionals will be collected as part of the baseline interview. Other patient characteristics including alcohol consumption (Alcohol Use Disorders Identification Test)
[54], psychological distress (the six-item version of the Kessler Psychological Distress Scale)
[55], and perceived levels of stress (the four-item version of the Perceived Stress Scale)
[56] will also be assessed at baseline and each of the follow-up points.

#### Intervention cost

Descriptive data on direct costs of the intervention will be collected as part of routine project delivery and administration throughout the project, and include all costs associated with inpatient and post-discharge intervention.

### Sample size

Considering 80% power with a 5% significance level, 332 participants per group will be required to detect a 4% difference (1% versus 5% for Normal and Supported Care participants, respectively) in prolonged abstinence at 12 months post-discharge. This sample size will also be adequate to detect a 10% difference in point prevalence abstinence at 12 months post-discharge
[20].

### Statistical analysis

Data will be analysed using IBM SPSS Statistics 22 (International Business Machines Corporation,
http://www-01.ibm.com/software/au/analytics/spss/).

Prior to any statistical analysis, baseline predictors of attrition will be examined. If it appears missing data are related to a measured aspect of the participants, those measures will be included as covariates in the hypothesis-testing models. The modelling strategy will allow the use of all collected data in our estimation. Sensitivity analyses will check that methods of dealing with missing data do not have a major impact on study conclusions. Outcome analyses, based on coding missing subjects as "smoking", will allow direct comparison of findings with the research literature.

#### Analysis of primary outcome measures

A linear model with estimation via Generalized Estimating Equations, using the logit link function given the dichotomous outcome variable, will be used to examine abstinence versus smoking status at 12 months by condition. The data collected at 1 and 6 months will also be examined; however, the 12-month follow-up will be the primary focus. Generalized Estimating Equations, a multivariate extension of generalised linear models, accounts for dependence of responses within individuals due to repeated measures. Any covariates identified in preliminary data analyses may be added to the model. Subgroup analyses will be considered, likely by dependence and diagnosis (psychosis versus non-psychosis)
[5,57]. All analyses will be conducted using intent-to-treat principles, with participants retained in their originally assigned groups
[58].

#### Analysis of secondary outcome measures

Chi square and *t*-test (or Mann–Whitney) analysis will be used to compare the number of quit attempts, nicotine dependence, cigarettes smoked per day, and motivation to change smoking behaviour between the intervention and control conditions. Descriptive statistics will be used to report process data.

## Discussion

Further research is needed to assess the effectiveness of a proactive and integrated approach to the provision of smoking cessation treatment to psychiatric inpatients immediately upon discharge, regardless of a patient’s assessed readiness to quit, in increasing abstinence and secondary smoking-related outcomes. This randomised controlled trial builds upon pilot work
[33], and incorporates enhanced elements including a larger sample size and greater statistical power, longer assessment of outcomes to 12 months post-discharge, use of a more structured motivational interviewing framework in the delivery of psychosocial support, and a more comprehensive and flexible NRT protocol in the delivery of pharmacological support.

The conduct of this trial and its findings will substantively strengthen the base of evidence available to inform the development and delivery of smoking cessation treatment to persons with a mental illness. It will hence contribute to redressing the significant health and social inequities experienced by this population sub-group as a consequence of tobacco smoking.

## Trial status

Recruitment for this project commenced in October 2012, with a plan to proceed until April 2014. Follow-up data collection has commenced; it is anticipated that it will conclude in June 2015.

## Abbreviations

CATI: computer-assisted telephone interview; NRT: nicotine replacement therapy.
